## Abstract

Active inference, a first-principles framework for modelling the behaviour of sentient agents, is beginning to be applied in consciousness research. One hypothesis arising from the framework is that active inference is necessary for changes in conscious content. As one component of an extensive adversarial collaboration among competing theories of consciousness, active inference will be contrasted with two other theories of consciousness, neither of which posit that active inference is necessary for consciousness. Here, we thus present a Study Protocol designed to test the active inference hypothesis using a carefully controlled adaptation of the motion-induced blindness paradigm, where an ‘active’ condition with richer active inference is contrasted with a ‘passive’ condition. In the active condition, participants direct their gaze towards a target stimulus following its disappearance from consciousness, and report on its subsequent reappearance. In the passive condition, participants maintain central fixation, while the stimulus array is moved across the visual field (in a replay of the active condition based on eye-tracking data acquired during active trials). In two experiments, we plan to investigate target reappearance across active and passive conditions to evaluate the contribution of active inference to conscious awareness. Results will eventually be considered in the context of all the experiments conducted as part of the overall adversarial collaboration.

## Introduction

Predictive processing theories of brain function and behaviour have accrued widespread interest in the cognitive sciences over the past two decades [1–5]. More recently, predictive processing has been advocated as a systematic foundation for the development of theories of consciousness [6–9]. In this Study Protocol, we describe two experiments designed to test a novel theory of consciousness, specifically a theory of changes in conscious content, derived from *active inference* (AI-C), a first-principles formulation of predictive processing. This theory will be contrasted with two other theories of consciousness, as part of an international adversarial collaboration led by the INTREPID consortium – one of five such projects funded under the Templeton World Charity Foundation’s ‘Accelerating Research on Consciousness’ initiative.

Active inference provides a normative framework for understanding how self-organising systems sample their world to resolve uncertainty and occupy their characteristic states [9–12]. Active inference (and the process theories that accompany it) conform to the free energy principle as an account of adaptive, self-organised behaviour [13,14]. In this perspective, autonomous agents (such as humans) act in ways that can be described as minimising a variational bound on free energy (surprise or self-information) over time, given a (generative) model of the probabilistic mapping between sensory outcomes and the latent states causing those outcomes. Such agents infer latent states and, crucially, infer policies for how to selectively sample sensory data that conform to their expectations of future sensory input, thereby accumulating evidence for their model and thus their own existence (cf. self-evidencing; [15]). The active sampling of sensory outcomes specified by an inferred policy forms a broad category of agency, which can occur in motor action, such as eye or head movement, or mental action, such as decisions to allocate spatial or feature attention.

In contrast to other theories of consciousness [16], such as theories in the predictive processing family, for example *neurorepresentationalism* (NREP) [17,18], and theories of different types, for example *integrated information theory* (IIT) [19,20], *global workspace* [21,22] and *higher order thought theory* (HOT) [23,24], active inference implies that active sampling of the sensorium, under an inferred policy, is aimed at reducing uncertainty about the causes of (actual or expected) sensations. For example, sampling in the visual domain through eye movements or other movement, or through mental active inference, namely selective attention allocation, would occur based on beliefs about the information gain enacting such policies would afford. Uncertainty reduction through active inference manifests as belief updating, which is hypothesised to underlie changes in conscious perception. There is reason to believe that active inference is implicated in conscious perception, since action imbues perception with a first-person perspective, and because active inference can help elucidate many findings in the science of consciousness, and help resolve various challenges in the field (for review, see [9]).

The active inference theory of conscious content (AI-C, hereafter) states that active inference is necessary for changes in conscious content; that is, if there is a change in conscious content, then there is active inference, and, equivalently, if there is no active inference, then there is no change in conscious content [8,9,25–32]. In a slogan, “to see is to look” – what is consciously ‘seen’ can only change when actively ‘looked at’ or ‘noticed’. Here, active seeing includes mental decision-making and planning such as selecting a policy for covertly attending to spatial location or object features (with concomitant disattention to other locations or features). Notice that this theory is minimal in the sense that it does not specify the sufficient conditions for the generation of conscious experience, leaving it open if other factors than active inference are needed. This theory contrasts to the other theories in this adversarial collaboration, NREP and IIT; these theories do not posit decision-making and planning in the motor or mental domains as a necessary condition on changes in conscious experience; that is, these competing theories allow changes in conscious content without the actions described formally in terms of active inference (though the theories naturally operate with different kinds of neural activity). The competing theories do recognize a role for action and attention in shaping conscious experience, such that what we look at or attend to help shape what we become conscious of, but they will appeal to theoretical constructs outside their core theoretical commitments in order to accommodate how attention and motor activity influence consciousness.

As described, AI-C says that active inference is a necessary condition for a change in conscious perception. On a strong reading, this theory would be challenged if a stimulus can become consciously perceived in the absence of active inference. This basic active inference hypothesis relates to conscious content and what mechanism underpins a change from seeing something to seeing something else (or from seeing nothing to seeing something). A corollary of this minimal active inference theory relates to the fact that abolishing all active inference for a participant is very difficult or may be impossible without rendering them wholly unconscious. This is because active inference includes a very broad category of activity, essentially any policy-guided gain control (or precision control) anywhere in a system such as the human brain (noting that this leaves room for many types of activity that are not formally speaking policy-guided, such as interpretation, imagery, and generation of top-down predictions). The corollary specifies what the theory implies for cases where active inference is diminished to some degree but not abolished, leading to the hypothesis that with less active inference or less confident (i.e., precise) active inference, change in conscious content will be hindered, slowed down or prevented. This consequence of the theory is motivated by the precision of the beliefs over policies, where policies with precise expected outcomes will garner more evidence for the beliefs in question. For example, if a policy of passively fixating—i.e., suspending active inference—is contrasted with a policy of actively foveating to a specific target, then AI-C predicts with strong confidence that conscious content should be facilitated in the latter case. It is this consequence of AI-C that will be tested in the experiments described in this study protocol. The competing theories, NREP and IIT, make predictions in the same direction or predictions of no change, and with less confidence, since they do not stipulate policy-guided action as necessary for a change in consciousness, but acknowledge that action may change conscious experience.

### Current study

Here, we describe a set of two experiments that form one of four Study Protocols (to be published separately), each of which is developed based on predictions of one of three major consciousness theories being tested in this adversarial collaboration (AI-C, IIT, and NREP).

As described above, the test of AI-C’s hypothesis proceeds by curtailing active inference in one, ‘passive’ condition, and contrasting that with an ‘active’ condition in which active inference leads to the selection of a policy of action with high expected information gain, with the prediction being that the active condition facilitates conscious awareness of the target. We will pursue this idea in a motion-induced blindness (MIB) paradigm, where a stationary peripheral target is rendered invisible due to the motion of a global pattern. We will contrast active sampling (via overt eye movement) with passive sampling (with eyes remaining at fixation) where, crucially, participants are exposed to identical visual input and retinal activation, and other task, attentional and expectation-related factors are kept constant. To assess the key prediction from AI-C that changes in conscious content will systematically occur earlier in the active condition, post hoc reports will assess whether the passively processed changes to sensory input are perceived later than the actively sampled changes.

In this study, we employ two experiments designed to assess these MIB active-passive differences (For more specific operationalised predictions relevant to the three theories considered in the adversarial collaboration (IIT, AI-C, NREP), see the section Operational Hypotheses below):

*Experiment A: Do changes in conscious experience occur earlier in the active than the passive condition?* This experiment will test whether the duration of MIB differs across the active and passive conditions. If there is no difference between conditions, or if MIB persists longer in the active condition, then that is strong evidence against AI-C. If MIB persists for longer in the passive condition, this would predominantly support AI-C.

*Experiment B: Does action improve sensitivity to backwards-masked stimuli?* This experiment combines MIB with a type of backward masking of the target stimulus. If the target is backwards-masked to preclude perception in the passive condition—by removing the target as it approaches the foveal region of the visual field—AI-C predicts that the target will still be perceived when the same masking setting is applied in the active condition. If there is no difference between conditions, or if the passive condition results in improved perceptual recognition, this would be evidence against AI-C; otherwise, this will provide evidence that action facilitates conscious awareness, and in that sense will predominantly support the active inference prediction.

Both experiments will also be equipped with measures of autonomic and neuromodulatory (i.e., cardiac and pupil) activity to adjust for any differences in attentional set (e.g., arousal) that could be considered to confound condition-specific differences. Further, in primates, attentional selective sampling under normal conditions is typically associated with motor activity (e.g., ballistic saccades or microsaccades, as well as eye blinks and pupil dilation and constriction), and therefore this study will record not only the saccades in the active condition (for play-back in the passive condition) but also microsaccades, pupil diameter and blinks throughout, in order to quantify differences between two conditions (such as microsaccades when fixating on the relevant location in both the passive and action conditions).

In the context of this Study Protocol, the conception of attention under active inference plays an important role in the overall dialectic. In the literature, several studies have investigated whether attention, as traditionally conceived, might dissociate from consciousness (for a review, see [33]). This research might contribute to the interpretation of findings from the current study, since if there are indeed changes in conscious perception without the attentional, mental action as conceived by active inference, then active inference would not be necessary for consciousness. For active inference however, attention (understood technically in terms of policy-guided precision control) forms a much broader category than in the standard literature, such that any kind of precision control, including motor active inference and any kind of mental active inference, technically counts as attentional processing. Therefore, for AI-C, findings to date suggestive of a dissociation would need to be discussed in the light of this broader conception of attention. Here it is plausible that AI-C would indeed be consistent with these findings, since active inference may still be in play in consciousness even if vernacular conceptions of attention are not – though a full case to this effect would have to be made. In the context of the present adversarial collaboration, this dialectic would unfold in terms of critical comparative analyses of the active inference conception of attention and the favoured conceptions of attention generated from the theory leads of NREP and IIT.

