### Participants, sample size, exclusion/inclusion criteria, and stopping rule

Experiments A and B will be conducted in parallel at the Monash Centre for Consciousness and Contemplative Studies, Monash University (Melbourne, Australia) and the Institute of Psychology, Friedrich Schiller University (Jena, Germany). Identical stimulus materials and programme scripts will be used to run the experiments on identical setups and under very similar circumstances.

Participants will be students and staff recruited through each institution’s internal recruitment system. The general public may also be recruited through email approaches based on flyer responses. Participants in Melbourne will be reimbursed for their time either with course credit or AUD$20-50; participants in Jena will receive a similar rate in Euros or partial course credits. Both research sites have received ethical approval from their respective University Human Research Ethics Committees (Monash Human Research Ethics Committee – Ethics Number: 29238; The Ethics Committee of the Friedrich Schiller University – Ethics Number: FSV 22/093.

Recent MIB work deploying eye-tracking and pupillometry in the MIB paradigm [36] aimed for a target sample size of 55 participants to give a statistical power of at least 80% with an effect size of η2p = .13.; we will adopt this sample size as a stopping point for data collection. Participants must have normal (or corrected-to-normal) vision and audition, and will be aged between 18 and 45 years. Additionally, participants must demonstrate computer literacy and be able to maintain constant fixation for at least 5 seconds in the pre-test period and follow the fixation-based gaze strategy. Respondents will be excluded from participation if they (1) report having previously suffered a stroke or other neurological condition; (2) are currently taking psychoactive medications; or (3) are currently undergoing mental health treatment.

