### Experiment A: Time to reappearance following motion-induced blindness

**Design, stimuli, and procedure.** This experiment deploys a within-subjects design to contrast differences in the time to reappearance of stimuli rendered subjectively invisible by MIB. The MIB task will be performed in conjunction with eye tracking in order to produce both active looking blocks and passive viewing blocks (where the active gaze is precisely replayed).

We will use the Racially Diverse affective expression (RADIATE) face stimulus set [37]. We use only neutral faces for our stimulus set, removing any stimuli with accuracy ratings for neutral emotional state below 80%. This leaves 108 stimulus images of distinct identities (and one used solely for instructional purposes). On each trial, the stimuli will be pseudo-randomly sampled with a constraint that no greater than two consecutive repetitions of a specific identity will be shown to participants. Each target stimulus will be converted to greyscale, scaled to 200x200 pixels, and luminance-matched using the SHINE toolbox [38]. All images will be enclosed in an elliptical mask centred on the face shape. In order to correct the luminance difference created by the mask the luminance of each stimulus image will be scaled to match an RGB value of 100 (+/- 0.1%); the background colour of the display will also be matched to this value.

Target stimuli will be presented at a randomly-selected polar angle (1–360 degrees) 9 degrees of visual angle from central fixation. In each trial, a blue central fixation dot will be present behind the stimulus and a cross pattern filling the entire screen will rotate at 2.7s/cycle, in line with previous work [39]. As the target in this design will either (in the passive case) remain stationary after being moved into central fixation or (in the active case) be foveated by the participant, it will ultimately fill the centre of the visual field in both conditions. This means that central attentional resources will eventually be allocated to it, and it will become visible even in the passive condition. This is consistent with active inference, since attention is a (covert) form of action. However, the thrust of this experiment lies in the role of overt action (eye movement), recognizing that covert attentional resources are also deployed in the passive condition at some point in the task.

Experiment A sessions will be separated into three sections:

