### Planned analyses and expected outcomes

In order to capture the contribution of covariates within both experiments, 3A and 3B dependent variables will be analysed under a generalized linear modelling framework based on a pre-specified decision tree (see Fig 3). The choice of link-function will be informed by the distributional properties of the data and the evaluation of standard model diagnostics (e.g., Q-Q plot of residuals) and indices of marginal likelihood (e.g., AIC). Nested model comparison will be used to evaluate whether model fit is significantly improved by the inclusion of focal parameters. Random effects and additional covariates accounting for potential sources of noise (e.g., mean inter-beat interval, time-on-task) may be included if warranted by theoretical considerations and model comparisons (for a similar approach, see [44]). As part of this analysis we will quantify microsaccades frequency and latencies, as well as pupil area trajectory. These findings will be included in the results and, if we find that any of these data features, when considering the period immediately following the cue, differ significantly between conditions we will include these as covariates in the model.

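### The plan counts a finding of no difference as strong evidence against AI-C, but its only stated test lets a merely non-significant result qualify

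*Protocol article*

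**What the plan says.** The protocol article, under Current study, sets out in advance how each result bears on AI-C. For Experiment A: "If there is no difference between conditions, or if MIB persists longer in the active condition, then that is strong evidence against AI-C". For Experiment B the wording is weaker: "If there is no difference between conditions, or if the passive condition results in improved perceptual recognition, this would be evidence against AI-C".

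The section Planned analyses and expected outcomes gives the only stated way of deciding whether the conditions differ: "Nested model comparison will be used to evaluate whether model fit is significantly improved by the inclusion of focal parameters".

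The section on participants and sample size takes its number from a recent MIB study, which aimed for a "target sample size of 55 participants" "to give a statistical power of at least 80% with an effect size of η2p = .13", and adds: "we will adopt this sample size as a stopping point for data collection".

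Tables 1 and 2 (Operational hypotheses) list no change as a permitted outcome for IIT and NREP but not for AI-C. AI-C's prediction is directional and carries no minimum size.

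**The concern.** A significance test that finds nothing shows only that the data did not reach the critical value. It does not show that the effect is absent or negligible. Because the nested comparison is the only stated route to a conclusion about a difference, a reader applying the plan would treat a non-significant condition term as no difference and then, in Experiment A, as strong evidence against AI-C.

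This matters because, apart from a reversal, a null is the only result in these experiments that AI-C's prediction excludes and the rival theories' predictions allow. It is the result for which a false conclusion costs most, and the plan gives it no error control.

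**Working it through.** **Inputs from the article.** N = 55; power of at least 80% at partial eta squared .13; a within-subjects active versus passive contrast.

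**Assumptions.** The article gives neither alpha nor sidedness, so 5% two-sided is assumed. Each participant is reduced to one paired difference, with the standardised paired difference dz set equal to Cohen's f. The planned trial-level mixed model may behave somewhat differently.

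**1. Reproduce the stated power.** f² = 0.13 / (1 − 0.13) = 0.1494, so f = dz = √0.1494 = 0.387. The noncentrality is 0.387 × √55 = 2.87 on 54 degrees of freedom. Noncentral-t power is 80.4%, and 55 is the smallest N that reaches 80%. The stated figure holds.

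**2. How often a real effect would be scored as no difference (N = 55).**

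| True dz | Power | Non-significant |
|---|---|---|
| 0.387 (planning effect) | 80.4% | 19.6% |
| 0.30 | 58.9% | 41.1% |
| 0.20 | 30.8% | 69.2% |
| 0.10 | 11.3% | 88.7% |

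Only the first row uses an effect given in the article. The others are illustrative, and are relevant because AI-C's prediction has no minimum size.

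**3. How much a non-significant result says.** It occurs with probability 0.95 if there is no effect and 0.196 at the planning effect, a ratio of 0.95 / 0.196 = 4.8. At dz 0.20 the ratio is 0.95 / 0.692 = 1.4.

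**4. What the interval still allows.** The 95% half-width is t(0.975; 54) / √55 = 0.270 SD of the differences. The planning effect stays inside the interval once the observed dz exceeds 0.387 − 0.270 = 0.117, and the result stays non-significant up to about 0.270. So observed values from about 0.12 to 0.27 are non-significant and compatible with the very effect the study was sized for.

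**5. A Bayes factor check.** With a default Cauchy prior (scale 0.707, a reviewer's choice), the Bayes factor for the null is 6.8 at t = 0, 4.2 at t = 1, 2.4 at t = 1.5 and 1.3 at t = 1.9. It stays below 10, an assumed threshold for strong evidence, even at an observed difference of exactly zero.

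**6. What the same data could show under a suitable rule.** If the true difference is zero, N = 55 has about 88% power (one-sided 5%) to exclude dz 0.387 in the predicted direction, and about 76% power for two-sided equivalence within ±0.387. The 90% interval half-width is 0.226, so the one-sided exclusion succeeds when the observed dz is below about 0.387 − 0.226 = 0.161. If the true effect equals the margin, this exclusion is wrong 5% of the time by construction. The 19.6% of misses in step 2 would then split into about 5% against and 19.6 − 5 = 14.6% inconclusive.

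**The case against.** The article says no difference, not non-significant, and says it in the Introduction, where it describes what each state of affairs would mean for the theory. A threshold may sit in the preregistration or in an analysis plan that is not shown. Both points are fair. Even so, the sentence fixes the strength of a conclusion, and the only test in the article is one of significance. A threshold elsewhere would still require this wording to be brought into line.

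A miss rate near 20% at the planning effect is ordinary 80% power, and with a one-sided 5% test it would be about 12%. That stands: the sample size is not at fault. The problem is the label put on the miss.

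Three stronger readings are tempting, and the document does not support them.

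- **That the design cannot yield evidence against AI-C.** It can, as step 6 shows. Against a point alternative of dz 0.387, the likelihood ratio for the null at t = 0 is about 61, so the Bayes factor ceiling in step 5 depends on the chosen prior.
- **That the arbitration among theories has a high uncontrolled error rate.** The section on the adversarial collaboration setting in the Introduction weighs results by preregistered confidences and defers judgement until all experiments are in. Operational hypotheses accepts that single experiments may not strongly separate the theories. These provisions limit the damage, but neither they nor the optional consortium-level Bayesian analysis defines no difference here.
- **That misses run at about 50% because each lab tests about half the sample.** The article separates the labs' analysis pipelines; it does not say that the 55 are divided for testing.

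**Conclusion.** The point holds in a limited form. For Experiment A the article labels a null as strong evidence against AI-C, and the test it states cannot separate a negligible effect from one that was missed. At the adopted effect, a true difference would be counted against AI-C about 20% of the time, and more often if the effect is smaller. For Experiment B the same logic applies at the weaker level of evidence against. The other half of each rule, a result in the opposite direction, is unaffected.

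The figures rest on a two-sided 5% paired test and dz = f. The sample-size statement itself is correct for the effect it names.

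**What to change.** Before results are seen, replace the rule for both experiments under Current study with three mutually exclusive outcomes, coding the predicted direction as positive (shorter time to reappearance in A, larger radius in B):

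1. **Supports:** a significant effect in the predicted direction.
2. **Against:** a significant effect in the opposite direction; or a non-significant result for which either the upper 90% confidence limit lies below a prespecified smallest effect that AI-C is taken to require, or a prespecified Bayes factor threshold for the null is met. The choice between the confidence limit and the Bayes factor should be fixed in advance.
3. **Inconclusive:** any other non-significant result.

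The planning effect, dz 0.387, could serve as the smallest effect, with about 88% power at a true zero. A smaller margin is harder to exclude with 55 participants: about 71% power at 0.30 and 43% at 0.20. Drop the word strong for mere non-significance. State that the against outcome reached through the margin excludes effects of at least the chosen size, not every directional effect.

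The cost is a few sentences and one added analysis per experiment, with no new data. Some results will be called inconclusive, and AI-C must commit to a smallest effect. Data collection is already under way, so the change should go promptly through the route in Dealing with amendments.
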